### Statistical analysis

Analyses will be performed in R (version 4.5.2) using RStudio (version 2025.09.2). All tests will be two-sided with α = 0.05. Baseline characteristics will be summarized using descriptive statistics.

The primary outcome (change in K-ADL from baseline to one year) will be evaluated in the overall cohort using a paired t-test or Wilcoxon signed-rank test, depending on distributional assumptions. Because the registry includes both newly enrolled and pre-existing patients, baseline functional status and prior exposure to KM-HMC services may differ between participants. Baseline characteristics, including baseline K-ADL, will therefore be compared between newly enrolled and pre-existing patients. To assess the robustness of the findings in the presence of this mixed cohort structure, a sensitivity analysis will be performed using multivariable linear regression with change in K-ADL as the dependent variable, adjusting for baseline K-ADL, months of prior service exposure, and registration status (new vs. existing). No interim analysis is planned.

Longitudinal NRS (measured at each visit) will be analyzed using a linear mixed-effects model with a random intercept and time treated as a continuous variable. Other secondary continuous outcomes (e.g., K-FRAIL) will be analyzed using paired t-tests or appropriate non-parametric alternatives.

Factors associated with response will be examined using multivariable logistic regression, with response operationally defined as a decrease of ≥1 point in the K-ADL score from baseline to 1 year. Participants who die or are permanently institutionalized during follow-up will be classified as non-responders to reduce attrition-related bias. Prespecified covariates are age, sex, comorbidity count, baseline K-FRAIL, baseline K-ADL, FTSST, baseline NRS, and service utilization frequency. Model fit, multicollinearity, and influential observations will be assessed using standard diagnostics.

Missing data will be handled using multiple imputation by chained equations (MICE), creating 20 imputed datasets and including auxiliary variables related to health status and service use; estimates will be pooled using Rubin’s rules. Exploratory analyses using administrative data (e.g., service utilization patterns and detailed assessments) will be conducted for hypothesis generation, with methods selected according to the research question and data structure.

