### Study design and setting

This is a multicenter, registry-based observational study collecting standardized baseline and follow-up data in routine practice; no study-mandated interventions or treatment restrictions will be applied. The protocol was prepared with reference to the SPIRIT (Standard Protocol Items: Recommendations for Interventional Trials) 2025 guidance, where applicable (S1 File. SPIRIT 2025 checklist).

The registry will be implemented at six KM-HMCs (Jungdong, Healthy Village, Dongbang Shintong Bubu, Haemalgeun, Kim Jeong-cheol, and Seohwa) participating in the national pilot project, selected to capture geographic variation. Under the pilot project, sites provide interprofessional home-based services that typically include at least monthly visits by KM doctors, twice-monthly nurse visits, and periodic social worker counseling.

KM-HMC services encompass comprehensive home-based primary care delivered in collaboration with community resources. In addition to Korean Medicine interventions (e.g., acupuncture, moxibustion, herbal medicine), services include a broad range of routine medical and nursing care such as wound care, catheter management, medication support, and monitoring of chronic conditions. Care is provided through coordination with local healthcare providers, nurses, and social welfare services, and may involve referral and linkage to community-based resources as needed. The specific components and frequency of care are individualized based on clinical judgment and patient needs.

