### Sample size

Because this is a registry-based observational study, the target sample size was set based on feasibility and the planned secondary analyses. Across the six participating sites, approximately 370 patients are expected to meet eligibility criteria. Assuming a participation rate of 70%, the registry aims to enroll approximately 250 participants. Allowing for 20% attrition due to mortality or institutionalization, the expected final analytic sample is approximately 200 participants.

For logistic regression of response, we prespecified response as a decrease of ≥1 point in the K-ADL score from baseline to 1 year. Because a validated minimal clinically important difference (MCID) for the K-ADL has not been established, this threshold was selected pragmatically, informed by indirect evidence from related basic ADL measures [12,13]. Based on this definition, we assumed a response rate of 35–45% according to a previous rehabilitation trial reporting recovery of ADL performance at 12 months [14]. With an expected final analytic sample of 200 participants, this would yield approximately 70–90 responder events, which is sufficient to support up to eight prespecified covariates based on an events-per-variable ratio of approximately 10 [15,16]. The prespecified covariates are age, sex, comorbidity count, baseline K-FRAIL, baseline K-ADL, Five Times Sit-to-Stand Test (FTSST), NRS, and service utilization, selected based on clinical relevance and prior evidence [17–20].

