### Outcomes

The primary outcome is the change in K-ADL from baseline to 1 year. K-ADL is a 7-item measure (score range 7–21), where lower scores indicate greater independence [18]. Secondary outcomes assessed at the 1-year interval include frailty status according to K-FRAIL (0: robust, 1–2: pre-frail, 3–5: frail) [17], changes in medication use (polypharmacy and deprescribing patterns), and patient satisfaction measured once at 1 year using the CSQ [21]. AIP indicators (mortality, long-term hospitalization >30 days, and admission to long-term care facilities) are recorded upon occurrence [22–24], while chronic pain intensity measured by the NRS (0–10) is assessed at every visit. Additional outcomes and covariates will be derived from pilot program–mandated administrative records, including the Comprehensive Assessment and Care Plan and visit logs, which capture sociodemographic characteristics, health and functional status, and service delivery details.

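### The NRS pain model names a random intercept but no random slope; if patients' pain courses differ or nearby readings correlate, it understates the standard error of the mean slope

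*Protocol article*

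**What the plan says.** The Statistical analysis section of the Protocol article fixes the pain model: the repeated NRS "will be analyzed using a linear mixed-effects model with a random intercept and time treated as a continuous variable". The same section sets the test level: "All tests will be two-sided with α = 0.05". For this model it mentions no random slope, residual correlation or robust variance. Its sentence on diagnostics follows the logistic regression of response.

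The Outcomes section says that "chronic pain intensity measured by the NRS (0–10) is assessed at every visit". Study design and setting describes services that "typically include at least monthly visits by KM doctors, twice-monthly nurse visits", with frequency adapted to the individual patient. Registry aims lists one-year change in chronic pain on the NRS among the secondary objectives. In this model the coefficient of time is the only term that can answer that objective.

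**The concern.** A random intercept lets patients differ in their level of pain but not in its direction. It also implies that, given the patient's level, two readings ten days apart are no more alike than two readings ten months apart. Under those assumptions each extra visit adds independent information on the mean slope, so the reported standard error keeps falling as visits accumulate. If slopes really differ between patients, one component of the true variance depends only on the number of patients and does not fall with more visits. The model leaves most of it out.

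The article itself gives grounds to expect differing slopes. The cohort mixes new patients with patients already under care, whose prior exposure may differ, and the content and frequency of care are individualized. For K-ADL the mixed cohort prompted a planned sensitivity analysis; none is described for NRS.

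At stake are the confidence interval and p-value for the pain objective. A change in mean pain could be declared more often than the stated 5% when there is none.

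**Working it through.** **Inputs from the article.** Two-sided α = 0.05. Analytic sample: 250 × (1 − 0.20) = 200, which reproduces the figure in Sample size. The article gives no SD, power or precision for the NRS slope, so there is no planned figure to reproduce for this model.

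**Visits per year (inferred).** Monthly doctor visits give 12 and twice-monthly nurse visits give 24: 36 if they never coincide and both professions record NRS, 24 if doctor visits coincide with nurse visits, 12 if only doctors record it.

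**Assumptions.** m complete, equally spaced visits over one year; normal, unbounded NRS; true mean slope 0; slope SD τ from 0 to 2 points/year; residual SD s from 1 to 2.

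**Formulas.** Let Stt be the sum of squared deviations of visit times from their mean, Stt = m(m+1)/[12(m−1)]. This is 3.171 for m = 36 and 1.182 for m = 12.

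- Standard error reported by the random-intercept model: √{[s² + τ²·Stt/(m−1)] / (N·Stt)}
- True standard error: √{τ²/N + s²/(N·Stt)}
- Actual type I error: 2Φ(−1.96 × reported/true)

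**Worked case: N = 200, m = 36, s = 1.5, τ = 1.**

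- Reported: √[(2.25 + 0.0906)/634.3] = 0.0607
- True: √(0.0050 + 0.00355) = 0.0925
- Ratio 0.66, so type I error = 2Φ(−1.29) = 19.8%

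**Type I error (%) by slope SD.**

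| Visits | Residual SD | 0 | 0.25 | 0.5 | 1.0 | 1.5 | 2.0 |
|---|---|---|---|---|---|---|---|
| 36 | 1.0 | 5.0 | 7.3 | 13.9 | 31.6 | 45.1 | 53.6 |
| 36 | 1.5 | 5.0 | 6.0 | 9.0 | 19.8 | 31.6 | 41.2 |
| 36 | 2.0 | 5.0 | 5.6 | 7.3 | 13.9 | 22.8 | 31.6 |
| 24 | 1.5 | 5.0 | 5.7 | 7.7 | 15.4 | 25.0 | 33.7 |
| 12 | 1.0 | 5.0 | 5.8 | 8.1 | 16.3 | 25.4 | 32.7 |
| 12 | 1.5 | 5.0 | 5.3 | 6.4 | 10.4 | 16.3 | 22.4 |
| 12 | 2.0 | 5.0 | 5.2 | 5.8 | 8.1 | 11.8 | 16.3 |

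N cancels from the ratio, so enrolling more patients does not help: N = 250 gives the same 19.8% in the worked case.

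**Simulation check** (4,000 runs per setting, N = 200, s = 1.5). At 36 visits the random-intercept test rejected in 5.0, 8.2, 20.2, 31.9 and 41.8% of runs for τ = 0, 0.5, 1, 1.5 and 2. A test allowing patient-specific slopes rejected in 4.5 to 5.2% at 36 visits and 4.8 to 5.9% at 12. Fitted mixed models at 36 visits and τ = 1 (100 runs) gave a mean reported standard error of 0.061 against an empirical SD of 0.091, with 19% rejections.

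**Serial correlation alone (τ = 0).** Take first-order autoregressive residuals with one-month correlation 0.2 and total variance 1 (the scale cancels).

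- 36 visits: adjacent correlation 0.2^(12/35) = 0.58. Reported slope variance per patient 0.927/3.171 = 0.292, true 1.005. Ratio 0.54, type I error 29%.
- 12 visits: adjacent correlation 0.2^(12/11) = 0.17. Reported 0.966/1.182 = 0.817, true 1.094. Ratio 0.86, type I error 9%.

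**The case against.** The strongest reply is that the article gives no slope SD, residual SD or serial correlation, so all of the inflation comes from assumed values. That stands. A reader might infer that the false-positive rate is simply well above 5%. The document does not support this: with a common slope and independent residuals the rate is 5%, and at slope SD 0.25 with independent residuals it is 5.2% to 7.3% across the settings tabulated.

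A reader might also take 36 readings a year as given. It is not. The article describes what services typically include, visits of the two professions may coincide, and it does not say that both record NRS. A range of 12 to 36 is what the text allows.

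A third reply is that covariance structures, robust variances and convergence rules are commonly left to the full protocol or analysis plan, neither of which is shown. That holds for those details, and their absence is not the finding. It does not cover the random-effects structure, which the article states, and nothing else in it amends that choice.

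Finally, the reach is limited. NRS is a secondary outcome in an uncontrolled registry. The paired K-ADL and K-FRAIL tests do not use this model, and the response model uses only baseline NRS.

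**Conclusion.** The point holds in conditional form. The stated model understates the standard error of the mean pain slope if patients' slopes differ or nearby readings are correlated, and the understatement grows with the number of visits. At least one of these conditions is likely in this cohort.

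The nominal 5% test has an actual error of about 5% to 54% at 36 visits and about 5% to 33% at 12, over slope SDs of 0 to 2 and residual SDs of 1 to 2 with independent residuals. At residual SD 1.5 and slope SDs of 0.5 and 1.0 it is 9.0% and 19.8% with 36 visits, and 6.4% and 10.4% with 12. Modest serial correlation alone gives about 29% and 9%. These figures assume complete, equally spaced visits.

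With balanced visits the slope estimate is not biased by this choice; only its confidence interval and p-value are affected. The change should be made, but it does not touch the primary analysis.

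**What to change.** In Statistical analysis, specify the NRS model with a random intercept and a random slope for time, and state that patient-clustered robust standard errors will be reported for the time effect. The random slope deals with differing pain courses. The clustered standard errors also cover serial correlation, which a random slope alone does not fully address, and they serve as the fallback if the slope model does not converge.

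This takes a sentence of text and a small change in model code, with no new data. The only cost is a wider, correct confidence interval. Data collection is scheduled to run to October 2027, so the change can still be prespecified.

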### Safety considerations

As an observational registry without experimental interventions, study-related risk is expected to be minimal. Mortality, long-term hospitalization (>30 days), and admission to a long-term care facility will be tracked as key events relevant to safety and sustainability. If such an event occurs, follow-up will be discontinued and the reason recorded in the CRF. Given the minimal-risk nature of the study, a formal data monitoring committee will not be convened; safety oversight will be conducted through regular investigator meetings and the independent monitoring process described above.

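### The non-responder rule covers fewer events than those that end follow-up, so some participants with no planned 1-year K-ADL fall to imputation and could be counted as responders

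*Protocol article*

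**What the plan says.** Four statements in the protocol article bear on this point.

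- **Safety considerations** names three events: "Mortality, long-term hospitalization (>30 days), and admission to a long-term care facility will be tracked as key events relevant to safety and sustainability". It continues: "If such an event occurs, follow-up will be discontinued and the reason recorded in the CRF".
- **Outcomes** lists the same three as separate items: "AIP indicators (mortality, long-term hospitalization >30 days, and admission to long-term care facilities) are recorded upon occurrence". Neither section limits facility admission to permanent stays.
- **Statistical analysis** sets the rule for the response endpoint: "Participants who die or are permanently institutionalized during follow-up will be classified as non-responders to reduce attrition-related bias". It does not name long hospitalisation, and the article does not define *permanently*.
- **Statistical analysis** then says: "Missing data will be handled using multiple imputation by chained equations (MICE), creating 20 imputed datasets". Auxiliary variables on health status and service use are to be included. No exception is stated for participants whose follow-up was ended by an event.

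The endpoint itself is fixed in the Sample size section: "we prespecified response as a decrease of ≥1 point in the K-ADL score from baseline to 1 year".

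**The concern.** A rule that counts certain losses as failures works only if it covers the losses that the design creates. Here the design creates three kinds, and the rule covers one fully, one in part, and one not by name. A participant in hospital for 31 days is discontinued, has no planned 1-year K-ADL and is not assigned non-response. A participant admitted to a facility is discontinued too, and is a non-responder only if someone judges the stay permanent. The article gives no definition of that judgement and no procedure for making it once follow-up has stopped, so two analysts could code the same admission differently.

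The rule exists to limit attrition bias. With this gap, a participant with one of the registry's own adverse aging-in-place outcomes may enter the response model with an imputed improvement. Both the response rate and the odds ratios for factors associated with response depend on how these participants are coded.

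**Working it through.** **Step 1. Set the lists side by side.**

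| Event | Ends follow-up (Safety considerations) | Aging-in-place indicator (Outcomes) | Non-responder by rule (Statistical analysis) |
|---|---|---|---|
| Death | yes | yes | yes |
| Hospitalisation >30 days | yes | yes | not named |
| Facility admission, judged permanent | yes | yes | yes |
| Facility admission, not judged permanent | yes | yes | no |

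Rows 2 and 4 have no planned 1-year K-ADL and no assigned outcome. The only remaining instruction that reaches them is the general one on missing data.

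**Step 2. What imputation can learn from.** Each of the three events ends follow-up, so observed 1-year K-ADL comes almost entirely from participants without such an event. The imputation model has essentially no K-ADL measured after a long hospital stay or facility admission. Auxiliary variables may lower the imputed chance of response, but they cannot be expected to bring it to zero.

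**Step 3. Reproduce the plan's figures (Sample size section).**

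- Enrolment: 370 × 0.70 = 259, stated as about 250. This is a rounded feasibility target and does not matter here.
- Analytic sample: 250 × (1 − 0.20) = 200, as stated. Expected losses: 250 − 200 = 50.
- Responders: 200 × 0.35 = 70 and 200 × 0.45 = 90, as stated.

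**Step 4. Size of the gap.** Let *s* be the share of the 50 losses that the rule does not cover. The article does not give *s*, so the values below are assumptions. Take the imputed response probability *p* as the plan's 35–45%. Extra responders = 50 × *s* × *p*.

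If all 50 losses are non-responders, the rate among 250 is 70/250 = 28% to 90/250 = 36%.

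| *s* | Uncovered participants | Extra responders | Responders in total | Rate among 250 |
|---|---|---|---|---|
| 10% | 5 | 1.75–2.25 | 71.75–92.25 | 28.7–36.9% |
| 20% | 10 | 3.5–4.5 | 73.5–94.5 | 29.4–37.8% |
| 50% | 25 | 8.75–11.25 | 78.75–101.25 | 31.5–40.5% |

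The relative increase is 50*s*/200: 2.5%, 5% and 12.5% in the three rows.

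**Step 5. Effect on the odds ratios.** An illustrative simulation used one covariate with an odds ratio of 0.67 for K-ADL response. The covariate also raised the chance of long hospitalisation, which was set at 4–12% of the cohort. All of these inputs are assumed. The fitted odds ratio was 0.59–0.66 with hospitalised participants coded as non-responders, and about 0.67 when they were imputed. The coding choice therefore moves the factor estimates as well as the rate. The simulation does not show that one of the two is wrong: they answer different questions.

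**The case against.** **The word may be meant loosely.** The Sample size section attributes all expected losses to mortality or institutionalisation, and the Discussion uses similar shorthand. Read that way, institutionalisation might include long hospital stays. But the Introduction, Registry aims, Outcomes and Safety considerations sections all list hospitalisation separately. Even on the loose reading, a 31-day stay is not permanent, so the gap remains.

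**Permanence may be known.** A reader might infer that sites can never learn whether a stay became permanent. The article does not support that. It says the reason is recorded, not that nothing else is, and it also draws on administrative records and visit logs. What stands is narrower: the term is undefined and no procedure for establishing it is stated. A definition may sit in the full protocol, which is supplied as supplementary files not seen here, but it would not bring non-permanent admissions within the rule.

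**Imputation of these participants is not stated outright.** This is correct. It follows from the unrestricted wording on missing data. The planned sample of 200 after attrition could also fit excluding them. However, the Statistical analysis section keeps deaths and permanent institutionalisation in the model as non-responders, so exclusion is not its stated approach to such losses.

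**An imputed responder is not necessarily a false one.** This stands. Someone hospitalised for 31 days could have a lower K-ADL at one year, and whether the event should count as failure is a choice of estimand. The argument rests on consistency: the plan has already chosen to count such losses as failures and applies that choice to only some of them.

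**The remedy changes the endpoint.** Dropping *permanently* makes short facility stays non-responses. That is a real cost, stated with the fix.

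**Conclusion.** The point holds as an internal mismatch. The events that end follow-up and the events assigned non-response are different lists, and the difference partly defeats the rule's stated aim. The mismatch is explicit in the text; that some of these participants would be counted as responders is an inference from the wording on missing data.

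The likely size is modest: about 2–11 extra responders against 70–90 planned. This assumes that 10–50% of the 50 expected losses are uncovered and that they are imputed at 35–45%. The upper end needs half of all losses to escape the rule, and the auxiliary variables could reduce the figure.

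A reader might infer that the main result is at risk through this rule. It is not: the rule governs the response rate and the logistic regression, which are secondary, and the primary paired K-ADL comparison does not use it. The point should be corrected, but it does not undermine the study.

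**What to change.** Use the same three events in Outcomes, Safety considerations and Statistical analysis, and replace the classification sentence with wording such as:

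> For the response endpoint, participants whose follow-up ended through death, hospitalisation of more than 30 days, or admission to a long-term care facility will be counted as non-responders before imputation. Multiple imputation will be used only for K-ADL missing for other reasons.

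Add one sensitivity analysis that treats participants hospitalised for more than 30 days or admitted to a facility as missing and imputes them, so that the effect of the classification can be seen.

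**Cost.** A few sentences of analysis wording, with no new data and no change to care. The response rate may be slightly lower, and short facility stays count as non-response.

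**Timing.** Enrolment opened on 5 November 2025. If the year runs from enrolment, the first 1-year assessments fall due about November 2026, so a change made before then would precede any 1-year outcome.

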### Data collection and management

#### Data collection and quality control.

Data entry follows a two-step process: (1) completed paper CRFs and de-identified copies of relevant administrative records (study ID only) will be securely transferred to the Central Data Management Team at Dongshin University; and (2) the central team will check for completeness and consistency and enter the data into a web-based electronic CRF system (iClick, managed by the National Institute for Korean Medicine Development).

To reduce inter-rater variability and maintain consistency across sites, all evaluators will complete standardized training before study initiation, including standard operating procedures for K-ADL, K-FRAIL, and other assessments. Inter-rater reliability will be assessed early in the study. Data monitoring will be conducted by an independent, monitoring-trained KM doctor via on-site visits, which will include a comprehensive review of all source documents. To minimize attrition, staff will build rapport during regular visits and conduct prompt telephone follow-up after missed appointments to reschedule visits and address barriers to continued participation.

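### Measurement error biases the baseline K-ADL odds ratio in the response model: treat it as adjustment only, and check K-FRAIL and FTSST with a refit

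*Protocol article*

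**What the plan says.** The Statistical analysis section of the protocol article sets the purpose of the model: "Factors associated with response will be examined using multivariable logistic regression". The outcome of that model is tied to the same baseline score that later serves as a covariate: "response operationally defined as a decrease of ≥1 point in the K-ADL score from baseline to 1 year". The covariate list follows: "Prespecified covariates are age, sex, comorbidity count, baseline K-FRAIL, baseline K-ADL, FTSST, baseline NRS, and service utilization frequency". The Sample size section repeats the response definition and opens the same list: "The prespecified covariates are age, sex, comorbidity count, baseline K-FRAIL, baseline K-ADL". It also says that the 1-point threshold is pragmatic, because no validated minimal important difference exists for K-ADL.

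The testing level is general: "All tests will be two-sided with α = 0.05". On sample size, "the expected final analytic sample is approximately 200 participants".

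On measurement quality, the Data collection and quality control section plans rater training and adds: "Inter-rater reliability will be assessed early in the study". It gives no reliability value and does not carry the result into the analysis. The article nowhere marks baseline K-ADL as adjustment only, and it does not mention regression to the mean.

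**The concern.** The baseline K-ADL reading is one half of the outcome and also one of the eight variables examined against it. A patient scored a point too dependent at baseline has a higher covariate value and a better chance of an apparent 1-point fall. An odds ratio of 1 for baseline K-ADL therefore does not mean that true improvement is unrelated to baseline function; it would only if K-ADL were read without error.

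Error is plausible here. There are six sites, proxy answers are allowed, and the threshold is the smallest step on the scale. The planned diagnostics (fit, multicollinearity, influential observations) would not reveal the problem.

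At stake is a stated secondary objective. The registry could report that more dependent patients respond better when nothing but reading error produced the result. The article says its findings may inform refinement of the care model.

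**Working it through.** **The plan's own figures.** 250 × 0.80 = 200 participants. 200 × 0.35 = 70 and 200 × 0.45 = 90 responders. Over eight covariates, 70/8 = 8.75 to 90/8 = 11.25 events per variable. These reproduce, and the point does not turn on them.

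**Algebra.** Let observed baseline be X = T + e0 and observed 1-year score Y = T + D + e1, with T true function, D true change and independent errors.

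- The observed drop is X − Y = e0 − e1 − D. If D is independent of T, Cov(X, X − Y) = Var(e0), which is positive whenever there is error.
- The linear slope of the drop on X is Var(e0)/Var(X) = 1 − reliability. That is 0.05, 0.10 and 0.20 points of apparent improvement per baseline point at reliability 0.95, 0.90 and 0.80.
- Add a covariate F (K-FRAIL or FTSST, higher = worse) that is related to T but not to D. Its coefficient is −Var(e0)·Cov(T,F) / [Var(X)·Var(F) − Cov(T,F)²]. This is negative, and it is zero if there is no error or no correlation.
- Example with true SD 3, reliability 0.90 and correlation 0.5: Var(e0) = 9 × 0.1/0.9 = 1.0; Cov(T,F) = 0.5 × 3 = 1.5; coefficient = −1.5/(10 − 2.25) = −0.19 points per SD of F.

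**Simulation of the logistic model.** From the article: 200 participants, response = drop of at least 1 point, two-sided 0.05, integer scores from 7 to 21. Assumed, not in the article: K-ADL mean 13 and SD 3; true-change SD 2, independent of every covariate; correlation 0.5 of K-FRAIL and FTSST with true K-ADL; reliability as shown. Ranges are over repeated simulations. Response rates were 40–44% where reported, inside the plan's 35–45%.

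| Reliability | Baseline K-ADL significant | K-FRAIL or FTSST significant |
|---|---|---|
| 0.999 | 5–8% | 5–6% |
| 0.95 | 15–19% | 7–9% |
| 0.90 | 41–44% | 12–14% |
| 0.85 | 65–69% | 17–18% |
| 0.80 | 80–83% | 24–29% |

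The first row shows that measurement error is the cause. The floor at 7 is not: excluding patients with a baseline of 7 leaves the pattern in place.

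**Sensitivity to the assumptions.**
- True-change SD 1.5, all eight covariates, reliability 0.95, 0.90 and 0.80: baseline K-ADL odds ratio 1.10–1.12, 1.15–1.18 and 1.19–1.27 per point, significant in 37–42%, 60–72% and 86–96%. K-FRAIL and FTSST: 6–9%, 9–15% and 10–27%. At reliability 0.95 and correlation 0.3 they are near nominal (6–7%).
- Narrower K-ADL spread (mean 14, SD 1.8), same reliabilities: baseline K-ADL 23%, 45% and 84%.
- 250 enrolled with a random 20% counted as non-responders, reliability 0.90: baseline K-ADL 39% (true-change SD 2) or 69% (SD 1.5).
- Perfect reliability, true-change SD 1.5: 6% without the scale limits and 11% with them, so the limits add a little of their own.
- An independent second baseline reading as the covariate (reliability 0.80–0.90, no attrition): odds ratio 1.00–1.02, significant in 4–6%. This confirms that the shared reading is the source.

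**Check of possible remedies.** A refit without baseline K-ADL returns K-FRAIL and FTSST to 4–7% when true change does not depend on baseline. If true change does depend on it (slope −0.2 per point), the refit rejects a null covariate in 8–16%, because baseline function now confounds. Requiring significance in both fits is costly: with that slope and a real covariate effect, power falls from 67–80% to 23–31%.

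**The case against.** **The model describes observed response.** Response is operationally an observed drop, and baseline K-ADL really is associated with that. Adjusting for baseline is not wrong in itself, and the Discussion presents the covariates as a guard against confounding. All of this stands, and it is why the variable should stay in the model. It does not cover reading the odds ratio as information on who improves, which the purpose of the analysis invites.

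**The size is assumed.** Reliability, the K-ADL spread, the SD of true change and the correlations are not in the article, and rater training may keep reliability high. This also stands. With true-change SD 2, reliability alone moves the K-ADL figure from about 15% to about 80%. Yet even at 0.95 the rate is about three times nominal or more.

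**It is secondary, and a fuller protocol exists in the supplementary files.** Agreed on the grade. But the article itself fixes outcome, covariates and purpose, so the combination is not a detail left open.

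**Stronger readings to avoid.** A reader might infer that the model will probably report frailer or slower patients as responding worse. The figures do not support that: the rate is 7–29% in the main setting and below one half even in adverse ones (46% at correlation 0.7). A reader might also infer that baseline K-ADL should be dropped, or that the primary result is in doubt. Neither follows: dropping it brings confounding, and the paired test uses no covariates.

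**Conclusion.** The point holds for baseline K-ADL. As specified, its odds ratio is pushed above 1 by measurement error alone, and the 5% test is no test of whether true improvement depends on baseline function. The effect is material across reliability 0.80–0.95 under the stated assumptions. The effect on K-FRAIL and FTSST is real in direction but smaller, and it is near nominal when reliability is high or their correlation with K-ADL is low. It calls for a sensitivity analysis, not a change of the main model. This is a should-fix matter for a secondary objective.

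**What to change.** In the Sample size and Statistical analysis sections:

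1. Keep baseline K-ADL in the response model as an adjustment term only. State that its odds ratio will not be reported or interpreted as a factor associated with response.
2. Keep the planned model as the main analysis for K-FRAIL and FTSST. Report beside it, as a sensitivity analysis, their odds ratios from a refit without baseline K-ADL.
3. State how to read the pair: an association seen only with baseline K-ADL in the model may reflect measurement error, and the refit may be confounded by baseline function. Do not require significance in both fits.
4. Optionally, use the planned inter-rater reliability to illustrate the size of the artefact, noting that it omits day-to-day variation within patients.

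Substituting the functional record from the Comprehensive Assessment is not a safe shortcut. For existing patients it dates from the start of home care (Study procedures), and the article does not show that it holds a comparable reading.

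The cost is wording and one extra model fit on data already planned. Baseline K-ADL is no longer offered as a reported factor.
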